### Participants

#### Parkinson’s Disease Patients

##### Inclusion criteria

•Patients with PD diagnosed according to the UK Parkinson’s Disease Society Brain Bank diagnostic criteria.•Age 55–75 years old.•Hoehn and Yahr (H&Y) score of 1–3.•20≤ Montreal Cognitive Assessment (MoCA) score ≤25.•Ability to walk and exercise independently.

##### Exclusion criteria

•Tai Chi or other exercise habits.•Other diseases that could interfere with conduct of the study protocol.•History of head injury.•Other significant psychiatric, neurological, or systemic comorbidity.•Magnetic Resonance Imaging (MRI) signal abnormalities (such as cerebral vascular lesions, white matter hyperintensities, and evidence of space-occupying lesions) or artifacts.•Severe cognitive, visual, or auditory impairment.•Depression or anxiety.•Deep brain stimulation.•MRI contraindications.•Alcohol or drug dependency or abuse.

#### Healthy Controls

##### Inclusion criteria

•Age 55–75 years old.•Ability to walk and exercise independently.

##### Exclusion criteria

•Tai Chi or other exercise habits.•Other diseases that could interfere with conduct of the study protocol.•History of head injury.•Other significant psychiatric, neurological, or systemic comorbidity.•MRI signal abnormalities (such as cerebral vascular lesions, white matter hyperintensities, and evidence of space-occupying lesions) or artifacts.•Severe cognitive, visual, or auditory impairment.•Depression or anxiety.•MRI contraindications.•Alcohol or drug dependency or abuse.

### Sample Size Calculation and Blinding

Sample size estimation was performed by G^∗^power V3.1 software (Franz Faul, Universitat Kiel, Germany). According to the analysis, at least 44 participants should be recruited (22 participants per group) in order to be able to perform two-factor repeated ANOVA (within-between interaction) with a middle effect size of 0.25 (Cohen, 1988), level of significance of 0.05, and power of 95% (Mayr et al., 2007). Since some participants may need to be dropped from the analysis due to excessive head motion during scanning, 40 participants will be recruited for each PD subgroup and 40 HC will be recruited. According to a similar studies published recently (Fiorenzato et al., 2019; Chen et al., 2021), this sample size should be adequate for replicating the previous effects in Fiorenzato’s study. In order to attract more participants, we will offer generous compensation and long-term health guidance. Every participant will be offered with an individual exercise plan when the whole study was completed. Randomization of PD patients will be done at the website www.random.org. Two researchers will be trained to assess the outcomes, and they will be blinded to group and will not participate in any interventions.

### Interventions

Participants in all PD patients’ groups will be asked to record their exercise every day throughout the trial, including both in the laboratory and at home.

#### Wuqinxi Training

Participants in the Wuqinxi group will attend a 24-week Wuqinxi exercise program consisting of 90-min group sessions three times a week. Each session will begin with 10 min of warm-up consisting of a breathing exercise, slow walking, and range-of-motion exercises, followed by 60 min of core Wuqinxi exercise (see Figure 2) with a 10-min break in the middle and 10 min of cooldown session consisting of limb range-of-motion movements, sustained stretching, and relaxing. The warm-up will focus on breaking down the movements and getting familiar with the main points of the movements; the later three steps will focus on consistency of movement, fluency of gait, and balance of posture. Heart rates will be monitored throughout the session using Polar Team2 heart rate monitors (Polar Electro, Finland). The intensity and difficulty, timing and frequency of the exercise will be adjusted for each participant based on their heart rate. Participants will be encouraged to practice at home, but not to participate in other exercises during the 24-week intervention period.

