## Abstract

**Background:** Parkinson’s disease (PD) is a neurodegenerative movement disease that includes non-motor symptoms such as cognitive impairment. Long-term mind-body exercise has been shown to improve cognitive ability in PD patients, but the methods of assessment and intervention were inconsistent across studies. Wuqinxi is a mind-body exercise that is easy to learn, has few physical and cognitive demands, and is recommended for PD patients. Dynamic functional connectivity (DFC) has been associated with cognitive alterations in PD patients, but no studies have yet explored the effects of Wuqinxi on this association. The current protocol is designed to measure the effects of long-term Wuqinxi intervention on cognition in PD patients, and explore the underlying neural mechanisms through DFC.

**Methods:** A long-term single-blind, randomized trial will be conducted. PD patients and age- and gender-matched HC will be recruited; PD patients will be randomly assigned to either Wuqinxi or balance groups, and HC will all receive health education. The Wuqinxi group will receive a 90-min session of Wuqinxi intervention three times a week for 24 weeks, while the balance group will receive balance exercise instruction on the same schedule. Primary outcomes will include assessment of cognitive domains and dynamic temporal characteristics of functional connectivity. Secondary outcomes will include severity of motor symptoms, mobility, balance, and emotional state. Assessments will be conducted at baseline, at the end of 24 weeks of intervention, and 12 weeks after interventions have ended.

**Discussion:** This study will provide evidence to the effects of Wuqinxi exercise on cognitive improvements in PD patients from the perspective of DFC, and will contribute to the understanding of neural mechanisms underlying cognitive enhancement through Wuqinxi practice.

**Clinical Trial Registration:**www.chictr.org.cn, identifier ChiCTR2000038517.

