#### Balance Training

Participants in the balance group will attend a 24-week balance training exercise program consisting of 90-min group sessions three times a week. Each training session will start with a 10 min warm-up (same as wuqinxi training). Then a 30-min balance exercise will be performed twice, with a 10-min break in between. Training will include the following sections: (1) static balance training: standing on unstable surfaces to maintain postural control and progression to weight shifting; (2) dynamic balance training: postural control in standing position while adding upper limb and trunk movements; (3) balance strategy exercise: focus on hip strategy while maintaining ankle strategy and stepping strategy under interference in different directions; and (4) adaptation of varying base of support, and standing in a narrow space and on uneven surface (Atterbury and Welman, 2017; Li et al., 2019). Each training session will end with a 10-min cooldown session (same as wuqinxi training).

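### As written, home practice is encouraged and other exercise discouraged only in the Wuqinxi arm, so total exercise may differ between the two PD arms by an unknown amount and direction

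*Protocol article*

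**What the plan says.** The comparator is set up to have the same timetable as the Wuqinxi arm. The Abstract says that "the balance group will receive balance exercise instruction on the same schedule". The two arm descriptions agree: 24 weeks, three group sessions a week, 90 minutes each. Balance Training describes its core block in these words: "Then a 30-min balance exercise will be performed twice, with a 10-min break in between". It refers back to the Wuqinxi arm for the warm-up and again for the cooldown: "Each training session will end with a 10-min cooldown session (same as wuqinxi training").

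Two rules on exercise outside the sessions stand under Wuqinxi Training, in one sentence: "Participants will be encouraged to practice at home, but not to participate in other exercises during the 24-week intervention period". No weekly amount is attached to the home practice. Balance Training contains neither rule.

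The opening paragraph of Interventions is the only one addressed to both PD arms. It contains a diary and nothing else: patients are "asked to record their exercise every day throughout the trial, including both in the laboratory and at home". Among the exclusion criteria for PD patients is "Tai Chi or other exercise habits", which is applied at entry.

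The Abstract also states what the result is meant to show. The study "will contribute to the understanding of neural mechanisms underlying cognitive enhancement through Wuqinxi practice".

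**The concern.** An active comparator on an equal timetable is useful because it holds the amount of exercise roughly constant, so that a difference between arms points to the kind of exercise. The rules on exercise outside the sessions take effect after randomisation, so randomisation does not balance what they do to the amount of exercise. If one arm is told to add practice at home and to avoid other exercise, while the other arm is told nothing, the equal timetable no longer secures equal exercise.

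This matters for the planned interpretation. The Introduction itself cites evidence that regular exercise goes with less cognitive decline in PD. Amount of exercise is therefore a rival explanation for any difference in cognition or DFC between the arms, and the mechanistic reading announced in the Abstract would have to compete with it.

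**Working it through.** **Step 1. Check the plan's own session length (Wuqinxi Training and Balance Training).**

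- Wuqinxi: 10 warm-up + 60 core + 10 break + 10 cooldown = 90 min.
- Balance: 10 warm-up + 30 + 10 break + 30 + 10 cooldown = 90 min.

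Both reproduce the stated 90 minutes. Without the break, each has 80 active minutes.

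**Step 2. Scheduled total per arm.**

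- Sessions: 24 weeks × 3 = 72.
- Supervised time: 72 × 90 / 60 = 108 h.
- Active time: 72 × 80 / 60 = 96 h, or 3 × 80 = 240 min a week.

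The nominal schedule is equal. This is the timetable, not the dose delivered. Under Wuqinxi Training the article also says: "The intensity and difficulty, timing and frequency of the exercise will be adjusted for each participant based on their heart rate". No such adjustment is described for balance sessions.

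**Step 3. Compare the rules for exercise outside the sessions.**

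| Rule | Common paragraph | Wuqinxi Training | Balance Training |
|---|---|---|---|
| Daily exercise diary | yes, both PD arms | – | – |
| Home practice encouraged | no | yes, no amount | no |
| Other exercise discouraged | no | yes, for 24 weeks | no |
| Warm-up and cooldown | – | described | refers back to Wuqinxi |

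The article had a paragraph for common rules and a way of referring back from one arm to the other. It used neither for these two rules.

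**Step 4. Scale of a possible imbalance.** The document gives no home-practice amount, so the net weekly difference between arms, m minutes, is an assumption and can run in either direction. Extra hours over the intervention = 24 × m / 60. Share of scheduled active time = m / 240.

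| Assumed m (min a week) | Hours over 24 weeks | Share of 96 h |
|---|---|---|
| 0 | 0 | 0% |
| 10 | 4 | 4.2% |
| 30 | 12 | 12.5% |
| 60 | 24 | 25% |
| 120 | 48 | 50% |

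For illustration, a 10% imbalance needs 0.10 × 240 = 24 min a week, which is 24 / 7 = 3.4 min a day, or 24 × 24 / 60 = 9.6 h over the 24 weeks. The 10% mark is only a reference point; the document sets no threshold.

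**Step 5. Direction.** Encouraged home practice would raise the Wuqinxi total. Unrestricted other exercise could raise the balance total. The text does not say which would be larger.

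**The case against.** The strongest reply is that this is silence in a condensed article. Nothing says that balance patients may not practise at home, or that they may take up other exercise. The sentence in question speaks of participants without naming an arm, and the diary covers home exercise in both arms, so common rules may have been intended. The stated aim is the effect of the Wuqinxi intervention, which can reasonably include Wuqinxi done at home, and the claim of an equal schedule is met by the session timetable. Excluding people with exercise habits makes heavy outside exercise less likely, and the diary would record it.

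Much of this stands. The intention is open, and the size of any imbalance rests wholly on assumed minutes. It does not remove the point. The rule is stated, and it is placed in a section that opens with the Wuqinxi group. The balance section repeats other shared elements but not this one, so staff working from the text would instruct one arm only. The entry criterion does not govern what patients take up during 24 weeks. A diary shows an imbalance but does not prevent it.

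A reader might infer three stronger things that the document does not support:

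- **That the trial is biased in favour of Wuqinxi.** The direction is unknown, and no effect on an outcome can be derived.
- **That the randomised comparison is invalid.** It remains a fair comparison of the two programmes as delivered.
- **That supervised exercise is matched exactly and only home exercise can differ.** Only the nominal schedule is matched, because heart-rate adjustment of intensity, timing and frequency is described for the Wuqinxi arm.

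**Conclusion.** The concern holds in a limited form and should be fixed; confidence is medium. The nominal supervised schedule is equal at 96 active hours per arm, but the written rules for exercise outside the sessions are not the same in the two PD arms. If they are followed as written, a difference in cognition or DFC belongs to the whole Wuqinxi programme, home practice included, and cannot be assigned to type of exercise at equal amount.

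The size is unknown and may be zero. The 12.5% to 50% range follows only from assuming a net 30 to 120 minutes a week. The conclusion also assumes that the placement of the sentence reflects what patients will be told; if both arms get the same instruction in practice, what remains is a gap in wording.

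**What to change.** In the opening paragraph of Interventions, state for both PD arms:

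1. Home practice is limited to the arm's own exercise, with the same stated weekly amount in each arm, or there is none in either arm.
2. No other exercise is taken up during the 24 weeks.

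Report diary exercise minutes by arm, descriptively. If the rules already apply to both arms, one sentence saying so settles the wording. If they are kept for the Wuqinxi arm only, word the conclusion as whole Wuqinxi programme versus balance training.

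The cost is small: a change of wording, one added instruction to balance patients and a short descriptive table. No extra patients or visits are needed, and the diary already exists in both arms. Extending heart-rate adjustment to balance sessions is not part of this fix; the document does not give the numbers of monitors or staff, so its cost cannot be judged.

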**FIGURE 2 F2:**
[figure not shown]
Illustration of Wuqinxi exercise maneuvers. **(A,B)** Tiger exercise; **(C,D)** deer exercise; **(E,F)** bear exercise; **(G,H)** monkey exercise; **(I,J)** bird exercise. Written informed consent for publication of the pictures was obtained from the poster demonstrator.

#### Balance Training

Participants in the balance group will attend a 24-week balance training exercise program consisting of 90-min group sessions three times a week. Each training session will start with a 10 min warm-up (same as wuqinxi training). Then a 30-min balance exercise will be performed twice, with a 10-min break in between. Training will include the following sections: (1) static balance training: standing on unstable surfaces to maintain postural control and progression to weight shifting; (2) dynamic balance training: postural control in standing position while adding upper limb and trunk movements; (3) balance strategy exercise: focus on hip strategy while maintaining ankle strategy and stepping strategy under interference in different directions; and (4) adaptation of varying base of support, and standing in a narrow space and on uneven surface (Atterbury and Welman, 2017; Li et al., 2019). Each training session will end with a 10-min cooldown session (same as wuqinxi training).

#### Healthy Controls

Participants in the healthy control group will not receive any intervention exercise.

### Resting-State and Structural MRI Acquisition and Preprocessing

Resting state functional MRI data and 3D high-dimension T1 image will be collected using a 3T Siemens Magnetom Prisma MRI scanner. PD patients will take medication during MRI scanning to minimize movement artifacts and reduce discomfort. All participants will be instructed to keep their eyes open and focus on a white “+” on black screen, letting their minds wander and trying not to fall asleep during the 10 min 6 s resting state functional MRI scan (gradient echo/fast gradient echo pulse sequence: repetition time = 2000 ms; echo time = 30 ms; flip angle = 80°; matrix size = 106 × 106; number of slices = 62; and voxel size = 2.0 × 2.0 × 2.0 mm^3^ with no gap; number of total volume = 304). During the structural scan participants will be instructed to sleep (repetition time = 3130 ms; echo time = 2.98 ms; flip angle = 4°; matrix size = 256 × 256; number of slice = 176; voxel size = 1.0 × 1.0 × 1.0 mm^3^).

Data preprocessing will be conducted using the SPM12 package implemented in MATLAB R2019a^1^. Prior to preprocessing (1) the first four scans will be deleted from the resting functional volume; (2) functional scans will be realigned to the first volume to correct for interscan head motion; (3) functional scans will be segmented into gray matter, white matter, and cerebrospinal fluid using the Tissue Probability Map template; and finally, and (4) normalized into standard Montreal Neurological Institute space using non-linear transformations and spatially smoothed with a Gaussian smoothing kernel of 6 mm. Participants with head motion greater than 1 mm will be removed from the study (Liao et al., 2014).

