### Outcome Measures

All measurements will be conducted before the intervention begins (baseline), immediately after the 24 weeks of intervention, and 12 weeks after the intervention.

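### As worded, the 1 mm head-motion rule removes participants from the study rather than scans from the imaging analysis, and so could drop randomised patients from cognitive and motor comparisons that need no scan

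*Protocol article*

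**What the plan says.** The section *Resting-State and Structural MRI Acquisition and Preprocessing* ends with the rule "Participants with head motion greater than 1 mm will be removed from the study". The unit removed is the participant and the scope is the study. No visit is named.

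The only other mention is in *Sample Size Calculation and Blinding*: "some participants may need to be dropped from the analysis due to excessive head motion during scanning". It does not say which analysis is meant. Head motion is the sole reason given there for going from 22 per arm to the planned number: "40 participants will be recruited for each PD subgroup and 40 HC will be recruited".

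*Outcome Measures* fixes the timing: "All measurements will be conducted before the intervention begins (baseline), immediately after the 24 weeks of intervention, and 12 weeks after the intervention". The primary outcomes are MoCA, the five RBANS domains and the DFC measures. The secondary outcomes include UPDRS-III, TUGT and questionnaires.

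The clinical analysis section under *Application of DFC in Wuqinxi Intervention* compares the two PD arms over the three timepoints by two-factor repeated ANOVA. It contains no motion exclusion, and no statement that patients with high motion are kept.

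**The concern.** A rule on image quality should decide which images are usable. This one, read literally, decides who is in the trial. At least two of the three scans come after randomisation and treatment, so a patient could be lost from the cognitive and motor comparisons because of something measured after allocation.

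The document itself gives grounds for thinking that this variable is not neutral. It has PD patients scanned on medication partly to limit movement artefact, so it treats movement in the scanner as related to the disease. Its hypothesis is that Wuqinxi will change motor and cognitive impairment. If motion follows motor severity and one arm improves more, the arms could lose different numbers of patients, and different kinds of patients.

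Two things are at stake: valid MoCA and RBANS data thrown away without need, and a comparison that is no longer of the groups as randomised.

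**Working it through.** **1. The two statements side by side.** The preprocessing section removes the participant from the study. The sample size section drops the participant from an unnamed analysis. Neither is limited to DFC, and no section keeps a high-motion patient in the clinical comparison. The literal reading is therefore available to an analyst, and so is the imaging-only reading.

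**2. The plan's own sample size.** Inputs from the sample size section: "two-factor repeated ANOVA (within-between interaction) with a middle effect size of 0.25", alpha 0.05, power 95%, two arms. Three timepoints come from *Outcome Measures*. Not stated, so assumed: correlation between repeated measures rho = 0.5 and no sphericity correction.

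- Noncentrality = f² × N × m / (1 − rho) = 0.0625 × 44 × 3 / 0.5 = 16.5
- df1 = (2 − 1)(3 − 1) = 2; df2 = (44 − 2)(3 − 1) = 84
- Power = 0.956 at N = 44 and 0.946 at N = 42

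The stated 44 is reproduced. The planned margin is 80 − 44 = 36 of 80, or 45%. With all 80 PD patients kept, power is 0.999 on the same assumptions. The required number depends on the assumed rho: 60 at 0.3 and 84 at 0.

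**3. Possible sample loss (illustration).** The document gives no failure rate. Let q be an assumed failure rate per scan, with failures independent within a person and one failed scan enough for removal. The share kept over three scans is (1 − q)³.

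| q | Share kept | Left of 80 |
|---|---|---|
| 5% | 0.857 | 69 |
| 10% | 0.729 | 58 |
| 15% | 0.614 | 49 |
| 18% | 0.551 | 44 |
| 20% | 0.512 | 41 |
| 30% | 0.343 | 27 |

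The minimum of 44 is reached at q = 1 − (44/80)^(1/3) = 0.181. If failures are fully correlated within a person, the loss is just q (72 left at 10%). Counting only the two scans that certainly follow randomisation, the loss is 1 − (1 − q)²: 10%, 19% and 36% for q = 5%, 10% and 20%.

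**4. Possible bias (illustration).** Suppose motion and outcome are bivariate normal with correlation r, higher motion going with a worse outcome, and a fraction p of an arm is removed for high motion. The mean of those kept, in SD units, shifts by −r × φ(c)/(1 − p), where c = Φ⁻¹(1 − p). The factor φ(c)/(1 − p) is 0.195 at p = 10%, 0.350 at 20%, 0.497 at 30% and 0.720 at 45%. The shift in the arm difference is |r| times the difference between the two factors:

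| Removed, arm A vs arm B | r = −0.3 | r = −0.5 |
|---|---|---|
| 10% vs 10% | 0 | 0 |
| 10% vs 20% | 0.05 SD | 0.08 SD |
| 10% vs 30% | 0.09 SD | 0.15 SD |
| 20% vs 45% | 0.11 SD | 0.19 SD |

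In this model the shift favours the arm that loses more patients. Both r and the removal rates are assumptions.

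**The case against.** The best defence is context. The sentence closes the preprocessing section, after realignment, normalisation and smoothing and just before the DFC computation. There it reads naturally as imaging quality control, loosely phrased. The sample size section speaks of the analysis, not the study, which fits imaging-only exclusion. The clinical analysis section has no motion rule. All of this stands. A reader might infer that the plan definitely deletes the clinical outcomes of high-motion patients, but the documents do not establish that.

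Timing is also open. No visit is named, the document does not say that one failed scan removes a patient at every visit, and the order of randomisation and baseline scan is not given. Exclusion on a baseline scan taken before randomisation would leave the comparison intact. The 24-week and follow-up scans have no such escape.

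Several features could limit differential removal: scanning on medication, two supervised exercise arms on the same schedule, and Hoehn and Yahr stage 1–3 only. Differential removal is possible but not shown.

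Finally, the sample-loss figures rest on assumed, independent failures. If motion follows motor severity, failures would cluster within patients and the cumulative loss would be smaller. For DFC, a repeated-measures ANOVA ordinarily needs all three visits anyway, so that loss does not come from this sentence. These points stand too.

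None of them supplies the missing limit. The rule is stated affirmatively, and following it as written would discard usable primary-outcome data.

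**Conclusion.** The point holds as a fault of wording with a possible consequence for validity. The two sections describe the rule differently and neither confines it to DFC. Applied literally to a scan after randomisation, it would remove patients from the MoCA, RBANS, UPDRS-III and TUGT comparisons on a variable plausibly related to motor severity. Bias follows only if removal differs by arm and motion is related to outcome. Its size and direction cannot be derived from the document, and the shifts of 0.05 to 0.19 SD above show only what such assumptions would produce.

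Two stronger readings are not supported. One is that the randomised comparison is already broken; imaging-only exclusion may have been meant. The other is that the trial is underpowered; the stated 44 is reproduced with rho = 0.5, and the plan carries a 45% margin over it. Extra recruitment, however, protects power only. It does not correct selection after randomisation.

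**What to change.** Reword the preprocessing rule so that a scan with motion above 1 mm is excluded from the DFC analyses only. State that the participant stays in the study and that all cognitive, motor and questionnaire outcomes are analysed as randomised. Align the sample size section by naming the DFC analyses as those from which data may be dropped. Report motion exclusions by arm and visit. Settle this before any data are seen by arm.

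The cost is a sentence or two of text and a small table in the report, with no new patients or measurements. The downside is that the numbers analysed will differ between clinical and imaging outcomes, which the report must explain.

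A mixed model using every usable scan is an optional addition for DFC. It would replace the planned repeated-measures ANOVA there, so it is a separate choice of method that the fix does not need.
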